### **5.2. Number of Participants**

A total of thirty-two (32) neurotypical male / female participants will be included.

The ratio of female participants should be approximately 50%, to the extent possible.

### **5.3. Number of Study Centers**

The study will be performed at one (1) investigational site in Rennes (France).

### **5.4. End of Study Definition and Duration of Participation**

The end of the study is defined as the date of the last visit of the last participant.

The maximum duration of the study for a participant will be approximately 1 week between the screening / first test visit (D1 Visit 1) and the re-test visit (D8 Visit 2).

### **5.5. Identification of Source Data**

The source data will consist of the data generated on-site by the EEG, and other assessments, the questionnaires and the data collected in the Investigator's source data book.

## 6. STUDY POPULATION

Each participant must participate in the informed consent process. Participants will sign and date the informed consent form (ICF) before any procedures specified in this protocol are performed.

### 6.1. Inclusion criteria

Participants must satisfy all of the following inclusion criteria before being allowed to enter the study:

1. A signed and dated informed consent form before any study-specific screening procedure is performed,
2. Aged 18 to 45 year-old (inclusive),
3. Able to undergo study assessments and willingness to comply with study procedures.
4. Within the limit of allowed head circumferences (between 54 and 60 cm)

### 6.2. Exclusion criteria

If any of the following exclusion criteria apply, the participant must not enter/continue in the study:

1. Any hair style incompatible with the proper wearing of an EEG cap, which is required for good quality EEG recording;
2. A history of any neurological or psychiatric disorder;
3. Participation in an investigational drug or device study within 4 weeks, or five times the half-life (if it is a drug study) of the investigational molecule (whichever is longer), prior to the clinic visit. The participant must not take part in any other trial during the study;
4. Significant changes in the consumption of alcohol, caffeine, or xanthine-containing products within 48 hours prior to each visit of the study,
5. CNS-active medications within 4 weeks prior to the study,
6. Positive test for drugs of abuse or alcohol and/or substance abuse/dependence during the last 12 months;

### 6.3. Lifestyle restrictions

Participants will be instructed at the early information call to refrain from strenuous physical activity one day before and on the day of the clinic visit.

The participants will be requested to maintain a stable routine for 2 days until the first visit (D1 Visit 1).

### 6.4. Screen Failures

Screen failures are defined as participants who consent to participate in the clinical study but are not subsequently included, because they fail to comply with inclusion and exclusion criteria.

Individuals who do not meet the criteria for participation in this study (screen failure) may not be rescreened.

## 7. INVESTIGATED DEVICES

### 7.1. Device selection

The reference system chosen is the one mainly used for current clinical trials conducted through [CRO], i.e. the [standard EEG], and therefore provides robust references for comparisons.

Regarding the selection of the three tested devices, landscaping of currently available equipment on the market was performed. The final selection was done based on criteria related to operational performances and data quality as assessed in pilot experiments.

A full technical description, as well as detailed operational instructions will be provided in a study specific user manual, according to each device that is separate from this study protocol.

### 7.2. Standard EEG device

[Standard EEG description]

### 7.3. [Test device 1]

[Test device 1 description]

### 7.4. [Test device 2]

[Test device 2 description]

### 7.5. [Test device 3]

[Test device 3 description]

### 7.6. Method of Device Assignment

The participants will be randomized to each sequence according to a (4x4) Williams Latin square design. The EEG device sequences will be as follows:

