| Design: 
This study will be performed at a single center, in a Phase 1 unit and involve neurotypical female and male participants. The experimental environment is intended to mimic closely the conditions of a clinical trial, in order to allow for the identification of the ideal EEG system for future clinical trials.
 
The study will consist of two assessment visits per participant at the clinical site (initial test sessions at D1 Visit 1 followed by re-test sessions at D8 Visit 2, approximately one week later).
 
The participants will be informed of study specific lifestyle restrictions in a phone call before the first visit.
 
The staff will be trained on the study conduct, including dummy runs, before the first visit of the first participant.
 
At each assessment visit, each participant will perform EEG recordings using the 4 devices (test device 1, test device 2, test device 3 and the reference wet EEG cap) and each device session will consist of 4 separate EEG recording types: resting state, auditory oddball task (P300), visually stimulation (specifically targeting activity in the <math>\gamma</math> band), a controlled artefact session (investigating the sensitivity of the systems to a series of standardized actions known to generate EEG interferences). Ease-of-use and comfort questionnaires will be completed after each test session by the participant as well as the technician.
 
The sequence of EEG devices recorded within each participant will be randomized according to a Latin square design, and consecutive EEG recordings will be separated by half an hour.
 
The same order of EEG devices will be applied to both visits of each participant to minimize within participant variability.
 |                                                                                                          |                                                                                                                                                                                                                                                                                                                                                                                                                                                                                                                             |                          |                                                                                            |                       |                                                                                                   |                       |                                                                                                  |                       |                                                                                                  |

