### 3. **INTRODUCTION**

Electroencephalogram (EEG) assessments in clinical trials are performed using non-invasive scalp electrodes. These electrodes require the application of a highly conductive electrolytic EEG gel between the scalp and the electrode to obtain good contact and reduce the impedance of the skin-electrode interface. Preparing the wet EEG cap is a time-consuming procedure that can be burdensome for patients.

New EEG recording devices that use dry or semi-dry electrodes may substantially reduce the set up time and burden for patients and clinical sites, however their signal quality and comparability to the current standard are unclear.

The main objective of this study is to compare the quantitative performance in terms of signal quality of three EEG recording devices, their ease-of-use through clinical sites and study participant's comfort, versus the standard set-up of a wet EEG cap.

The objective of the study is not to perform any absolute assessment of the performance of the devices (each device has already been certified and is considered as fully functional). The purpose of this project is to compare each tested device to a reference EEG system.

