**Table 1: Randomization**

| Sequence | Session 1 | Session 2 | Session 3 | Session 4 |
|----------|-----------|-----------|-----------|-----------|
| 1 | A         | B         | C         | D         |
| 2 | B         | C         | D         | A         |
| 3 | C         | D         | A         | B         |
| 4 | D         | A         | B         | C         |

where A, B, C and D are the reference EEG wet cap, and investigated devices 1, 2 and 3, respectively. In case of incomplete groups of 4 participants, unused participant numbers will be discarded.

The participants' randomization list will be prepared by Biotrial EEG Corelab.

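### Section 7.6 names a Williams Latin square, but Table 1 is a cyclic square that is not balanced for the immediately preceding device

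*Protocol*

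**What the plan says.** Section 7.6 (Method of Device Assignment) names the design: "The participants will be randomized to each sequence according to a (4x4) Williams Latin square design". It presents Table 1 as the list of sequences. Read across the four sessions, the rows are ABCD, BCDA, CDAB and DABC.

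The key below the table reads "where A, B, C and D are the reference EEG wet cap, and investigated devices 1, 2 and 3, respectively". The Synopsis is less specific: "The sequence of EEG devices recorded within each participant will be randomized according to a Latin square design". It also says "consecutive EEG recordings will be separated by half an hour" and, for the second visit, "The same order of EEG devices will be applied to both visits of each participant to minimize within participant variability". Section 5.2 sets the size: "A total of thirty-two (32) neurotypical male / female participants will be included".

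**The concern.** A Williams square is chosen for one property beyond those of any Latin square: each device immediately follows each other device equally often. In a 4x4 square every one of the 12 ordered pairs occurs once. An effect of the preceding session is then spread evenly over the test devices and can be separated from the device effect at little cost.

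Table 1 moves each row one step along the same cycle, so a device that has a predecessor always has the same one. Device 1 is only ever preceded by the wet cap, Device 2 by Device 1, Device 3 by Device 2, and the wet cap by Device 3.

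Some carryover is conceivable here. Section 3 says of the electrodes in standard use: "These electrodes require the application of a highly conductive electrolytic EEG gel between the scalp and the electrode". The new devices use dry or semi-dry electrodes, and all four systems are worn on the same head on the same day. Signal quality is the primary objective and participant comfort a secondary one, and either could depend on what was worn just before. At stake is whether a difference between devices reflects the device or its fixed predecessor.

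**Working it through.** **Inputs**
- Sequences and device key: Protocol, Table 1.
- N = 32: Section 5.2.
- 8 participants per sequence (32/4): an assumption. It is implied by four sequences and by the rule "In case of incomplete groups of 4 participants, unused participant numbers will be discarded", but is not stated outright.
- Same order at Visit 2: Synopsis, Design.
- L, the shift that the wet cap causes in the next recording: not given, so kept as a symbol.

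**Step 1. Is the stated design reproduced?** Count the ordered adjacent pairs over the four rows (4 rows × 3 transitions = 12).
- Table 1: A→B = 3, B→C = 3, C→D = 3, D→A = 3, and the other 8 pairs = 0.
- Williams criterion: each of the 12 pairs = 1.

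Each device appears once in each session position, so Table 1 is a Latin square, but it is not a Williams square. None of the 24 relabelings of A–D makes it one.

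**Step 2. Who follows the wet cap?** Multiply the counts by 8.

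| | Immediately after wet cap | After wet cap at any earlier time that day |
|---|---|---|
| Device 1 | 3 × 8 = 24 of 32 | 24 of 32 |
| Device 2 | 0 of 32 | 16 of 32 |
| Device 3 | 0 of 32 | 8 of 32 |

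The proportions 3 of 4 sequences against 0 of 4 follow from Table 1 alone. In ABDC, BCAD, CDBA, DACB every ordered pair occurs once, so each test device immediately follows the wet cap in 8 of 32.

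**Step 3. Bias without a carryover term.** Suppose only the wet cap leaves an effect, only on the next session, of size L. The reference never follows itself, so the bias of a device-minus-reference contrast is L times the proportion of participants in whom that device immediately follows the wet cap.
- Table 1: Device 1 = (24/32)L = 0.75L; Devices 2 and 3 = 0. Between Device 1 and Device 2 or 3 the bias is 0.75L.
- Williams: (8/32)L = 0.25L for each test device. Between test devices it is 0.25L − 0.25L = 0.

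**Step 4. Precision.** The model is least squares with fixed participant, session-position and device effects for 32 participants at one visit, with and without a term for the preceding device. The variance of a device contrast is c′(X′X)⁻c, in units of the residual variance.

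| | No carryover term | With carryover term |
|---|---|---|
| Table 1 | 0.0625 (= 2/32) | 0.344 |
| Williams | 0.0625 | 0.069 |

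With the term, the variance ratio is 0.34375/0.06875 = 5.0 and the standard-error ratio is √5.0 = 2.24. All device contrasts remain estimable under both designs.

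**The case against.** The case on the other side has five parts.

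- **Carryover is unproven.** The protocol gives no value for L. It plans a half-hour separation, about 2 hours per session including set-up and clean-up (Section 10.4.1), and breaks. Procedures between sessions may be described in the separate EEG Manual, which is not at hand. This stands: L may be small, and 0.75L is a coefficient and not a demonstrated bias.
- **The precision loss is conditional.** The protocol commits only to univariate statistics and linear modelling. Without a carryover term the two designs are equally precise. This also stands. A reader might infer that the study has the information of only about six participants (32/5.0 = 6.4); that applies only if the term is fitted.
- **Devices 2 and 3 are not free of the wet cap.** A reader might infer that gel residue can reach only Device 1. The documents do not support that: later the same day Device 2 is recorded after the wet cap in 16 of 32 and Device 3 in 8 of 32. The zeros hold for the immediately preceding session only.
- **Repeating the order at Visit 2 is deliberate.** Test-retest reliability is a listed primary endpoint, and a fixed order keeps the two visits comparable for each device. Repetition fails to rebalance the predecessors, but it is not a separate error.
- **Table 1 is a valid Latin square and agrees with the Synopsis.** Deleting the word Williams would remove the contradiction. It would leave the predecessor imbalance in place.

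None of this reconciles the text of Section 7.6 with its table. Loss of table content in the PDF conversion is an unlikely explanation, because all four rows are complete and shift regularly.

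**Conclusion.** Wrong as written. Section 7.6 claims a design property that Table 1 lacks. The pair count needs no assumption: 4 of 12 ordered pairs occur, three times each, and 8 do not occur. The figures of 24, 0 and 0 of 32 assume equal allocation of 8 per sequence.

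Device and first-order carryover are heavily confounded. A reader might go further and call them aliased, but every device contrast can still be estimated after adjustment, with 5.0 times the variance that a Williams square would give. The unadjusted bias of 0.75L, 0 and 0 (against 0.25L for each test device in a Williams square) rests on an effect that comes from the wet cap alone and lasts one session. The documents do not show that such an effect exists or how large it is. The point is that the protocol names a safeguard against it that the listed sequences do not provide, and an analysis model cannot supply the missing pairs afterwards.

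**What to change.** Before the randomization list is generated, replace the four rows of Table 1 with a true Williams square, for example:

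- Sequence 1: A B D C
- Sequence 2: B C A D
- Sequence 3: C D B A
- Sequence 4: D A C B

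Assign 8 participants to each and state the equal allocation. Each device then takes each position once and each ordered pair occurs once. The same order may be kept at both visits. The Synopsis should name the same design as Section 7.6.

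The cost is four table rows and one randomization list, with no added participants, sessions or procedures. If enrolment has already begun, delete the word Williams from Section 7.6 and report the predecessor imbalance as a limitation, with the counts above.

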**Table 1: Randomization**

| Sequence | Session 1 | Session 2 | Session 3 | Session 4 |
|----------|-----------|-----------|-----------|-----------|
| 1 | A         | B         | C         | D         |
| 2 | B         | C         | D         | A         |
| 3 | C         | D         | A         | B         |
| 4 | D         | A         | B         | C         |

where A, B, C and D are the reference EEG wet cap, and investigated devices 1, 2 and 3, respectively. In case of incomplete groups of 4 participants, unused participant numbers will be discarded.

The participants' randomization list will be prepared by Biotrial EEG Corelab.

## 8. **PRIOR TREATMENTS**

No CNS-active medications are allowed during and 4 weeks prior to the study. Participants will be instructed to refrain from strenuous physical activity one day before and on the day of the clinic visit.

## 9. **DISCONTINUATION CRITERIA AND RELATED PROCEDURES**

### 9.1. **Withdrawal/Discontinued criteria**

A participant may withdraw their consent at their discretion.

Any participant may be withdrawn from the study at the discretion of the Investigator.

Participants withdrawn or discontinued from the study must not be reincluded.

### 9.2. **Replacement of study participants**

Participants that do not complete both visits will be replaced.

## 10. **PROCEDURES**

### 10.1. **Staff training**

Within the month prior to the start of the study, Biotrial EEG Corelab will organize a training session for the staff that will be performing the experimental procedures.

Each member of staff will perform a dummy run and answer a first questionnaire on their expectancies about the equipment, as shown in [Figure P1](#). The output of the dummy run will be assessed by the EEG Corelab referent in terms of compliance with the instructions.

### 10.2. **Investigational schedule**

The schedule of assessments is described in [Section 2](#), Schedule Of Activities (SOA).

### 10.3. **Screening Procedure**

The participants will be called 2 working days before the D1 Visit 1 and be informed of lifestyle restrictions prior to study inclusion.

On the day of screening, after the informed consent has been obtained as described in the Inclusion Criteria [Section 6.1](#) and [Appendix 1](#), the following information will be collected: medical history, demographic data, including name, gender and age, current lifestyle. Each participant will have an abbreviated physical examination, alcohol breath test and urine drug screen. Compliance with all inclusion and exclusion criteria will be verified.

Any given included participant will be followed by the same member of staff throughout the study.

### 10.4. **Performance Assessment**

#### 10.4.1. **Assessment Methods and Experimental Schedule**

All experimental procedures will be described in full depth in an EEG Manual accompanying this study protocol as separate document to support transparent and reproducible procedures.

**Figure P2: Timing of Tests during each session**[figure not shown]

The sessions will have the same order of tasks (as shown in [Figure P2](#)) which is:

- Resting State EEG: eyes open and eyes closed
- Visual Gamma-band stimulation
- P300 ERP
- Controlled artefact stimulation test

The overall length of a session for each device is planned to be approx. 2h, including set-up and clean-up time and questionnaire assessments. In between the active recording sessions breaks are planned as well to allow for participants to rest as appropriate., 10

#### 10.4.1.1. Resting State EEG

The resting state EEG will be the first record of each session, performed as detailed in the SOA in [Section 2](#). The procedure will overall yield 10-minutes of EEG recording including all EEG channels available on the acquisition system.

The resting-state EEG allows a quantitative measurement of neuronal activity at different frequencies, e.g., power in conventional frequency bands, in the absence of any specific task. Resting-state brain activity will be recorded in two conditions: (1) with eyes closed (5 minutes) and (2) with eyes open (5 minutes). During eyes open condition, participants will be asked to keep looking at a fixed target.

#### 10.4.1.2. Visual gamma-band stimulation

Participants are seated with EEG cap mounted and are instructed to sit still and relax. During the task, participants are presented with a visual stimulus consisting of circular, concentric, contracting high contrast sine wave patterns on an external monitor placed at around 69 cm of the participant (annular gratings) following Hoogenboom et al. (10.1016/j.neuroimage.2005.08.043). The annular gratings will have a size of 5 degrees visual angle. The spatial frequency will be 2 cycles per degrees, and the gratings will move at 3 cycles per second, with a contrast of 100%. A red dot will always be shown at the center of the screen for fixation. The participant must keep their gaze at this fixation point and will be asked to refrain from blinking. The stimulus is presented for one second and repeated 300 times between each stimulus, there is a blank period with only the red dot on the screen for a random duration of 1 second to 1.4 second. Spatial frequency and contraction speed are designed to induce reliable visual stimuli in the gamma band. The different grating parameters have been defined according to the publication *Localizing human visual gamma-band activity in frequency, time and space*.

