#### 4. OBJECTIVES AND ENDPOINTS

|                  | Objective                                                                                                                               | Endpoint                                                                                                                                                                                                                                                                                                                                                                                                                                                                                                                                          |
|------------------|-----------------------------------------------------------------------------------------------------------------------------------------|---------------------------------------------------------------------------------------------------------------------------------------------------------------------------------------------------------------------------------------------------------------------------------------------------------------------------------------------------------------------------------------------------------------------------------------------------------------------------------------------------------------------------------------------------|
| Primary   | To compare the quantitative performance in terms of signal quality between three new EEG systems and a standard clinical wet EEG system | 
 
- EEG features derived from resting state recordings
 
- Latencies and amplitudes of evoked components as well as Signal-to-Noise Ratio from an auditory oddball task
 
- Visual gamma activity (e.g. power and peak frequency)
 
- Test-retest reliability of all EEG derived features during resting state and task recordings
 
- Robustness to artefacts and non-neural signal sources
 
                                                                          |

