### **Visual gamma-band stimulation**

#### Raw data

- Time locked EEG responses to the onset and offset of visual grating stimuli during artefact free data epochs.

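### The visual gamma task asks participants not to blink through a continuous run of 10 to 12 minutes with no blink or rest period, which costs clean epochs for a primary endpoint

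*Protocol*

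**What the plan says.** Section 10.4.1.2 of the Protocol fixes the trial cycle. For the grating: "The stimulus is presented for one second and repeated 300 times". Between gratings, "there is a blank period with only the red dot on the screen for a random duration of 1 second to 1.4 second". The eye instruction is "The participant must keep their gaze at this fixation point and will be asked to refrain from blinking", and the fixation mark never leaves the screen: "A red dot will always be shown at the center of the screen for fixation". The section mentions no cue to blink, no division into blocks and no rest within the run.

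The rest periods that the Protocol does mention are elsewhere. Section 10.4.1 says: "In between the active recording sessions breaks are planned as well to allow for participants to rest as appropriate". Section 10.4.1.4 gives one minute of free rest between repetitions of the artefact blocks, and an on-screen cross that tells the participant when to blink.

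Section 4 lists visual gamma activity under the primary objective. In Section 10.4.2 its raw data are "Time locked EEG responses to the onset and offset of visual grating stimuli during artefact free data epochs". Test-retest reliability of the derived features from Day 1 to Day 8 is also planned.

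**The concern.** The blank shows the fixation dot and the request not to blink carries no exception, so the blank is not offered as a blink window. Few people can comply for more than ten minutes, and each participant is asked to do so eight times (four devices at two visits). Blinks will occur, and the task does nothing to steer them away from the parts of the cycle that are analysed. A blink during the grating contaminates the response. A blink in the blank contaminates the period before the next stimulus, which is the natural baseline.

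At stake is the number of usable epochs per recording. Fewer clean epochs make each recording's gamma estimate noisier, which lowers the precision of the device comparison and of the Day 1 to Day 8 reliability estimates. The loss is avoidable at little cost.

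**Working it through.** The Protocol states no run length for this task, so there is no figure of its own to reproduce.

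**Step 1. Run length.** Inputs from Section 10.4.1.2: 300 stimuli of 1 s, each with a blank of 1.0 to 1.4 s (mean 1.2 s).

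- Shortest: 300 × (1 + 1.0) s = 600 s = 10.0 min
- Mean: 300 × (1 + 1.2) s = 660 s = 11.0 min
- Longest: 300 × (1 + 1.4) s = 720 s = 12.0 min

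Counting 299 blanks instead of 300 gives 9.98 to 11.98 min. With four devices, the mean is 4 × 11 = 44 min of this task per visit.

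**Step 2. Epochs that contain a blink.** The documents give no blink rate, blink duration or epoch window, so all three are assumptions: blinks as a Poisson process at r per minute, blink width 0.3 s, and an epoch window w of 1.0 s (grating only), 1.5 s (grating plus 0.5 s baseline) or 2.2 s (whole mean cycle). Clean epochs = 300 × exp(−r/60 × (w + 0.3)).

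| r (per min) | w = 1.0 s | w = 1.5 s | w = 2.2 s |
|---|---|---|---|
| 1 | 294 (2% affected) | 291 (3%) | 288 (4%) |
| 4 | 275 (8%) | 266 (11%) | 254 (15%) |
| 10 | 242 (20%) | 222 (26%) | 198 (34%) |
| 15 | 217 (28%) | 191 (36%) | 161 (47%) |

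Across 4 to 15 per minute the share affected runs from 8% to 47%. If participants suppress blinking almost completely (1 per minute), it is 2% to 4%.

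**Step 3. What pauses could gain.** If every affected epoch were dropped, the standard error of one recording's trial average would vary as 1/√(clean epochs). A fall in blink rate of d per minute during trials then changes it by a factor exp(d × (w + 0.3)/120). With w = 1.5 s this is exp(0.015 × d):

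- d = 0 (pauses change nothing): 1.00
- d = 1 (5 to 4 per minute): 1.015
- d = 6 (10 to 4 per minute): 1.094
- d = 11 (15 to 4 per minute): 1.179

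The values of d are assumptions. Nothing in the documents says how far pauses would lower the rate.

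**Step 4. Effect on the endpoint.** Let f be the share of the endpoint's variance that is trial noise. The rest is variation between participants, sessions and electrode placements, which pauses do not touch. The standard error of the endpoint then changes by √(1 − f + f × k²), where k is the factor from Step 3. For illustration, with f = 0.3:

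- k = 1.094: √(0.7 + 0.3 × 1.197) = 1.029, about 3%
- k = 1.179: √(0.7 + 0.3 × 1.390) = 1.057, about 6%

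At the limits, f = 0 gives no effect and f = 1 gives the full 9% or 18%.

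**The case against.** The strongest reply is that the absence of a pause is read from silence. Section 10.4.1 defers full procedural detail to an EEG Manual, which is not shown, and to a timing figure, which is also not shown. The sentence there on breaks ends in a fragment, so its scope cannot be fully read. Pauses may already exist. This stands as a condition on the fix. It does not remove the point, because Section 10.4.1.2 describes the cycle and the eye instruction in detail and leaves no place for a pause.

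It can also be said that the Protocol does not rely on perfect compliance. Refraining from blinking is a request, only artefact-free epochs are used, and the Synopsis (Criteria for evaluation) says the amount of artefact-free data will be quantified and compared for all recordings. Section 10.4.2 refers to standard artefact cleaning, so some affected epochs may be recovered. All of this stands. It means that the shares in Step 2 are epochs affected, not necessarily epochs lost.

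A reader might infer three stronger things that the documents do not support:

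- **Blinks spread at random over the cycle**, so that about 45% (1/2.2) hit the grating. The timing is only uncontrolled. Participants may save blinks for the blank, which would concentrate the damage in the baseline.
- **A definite precision gain from adding pauses.** Any such figure needs a blink rate after the change, and none is available. Step 3 shows that the gain can be zero.
- **A biased device comparison.** Every participant receives the same instruction with all four devices. Retained data may differ by device where blinks are harder to separate, but robustness to artefacts is itself listed under the primary objective, so that difference is partly what the study sets out to measure.

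**Conclusion.** The point holds as an inexpensive improvement to the task. Nothing in the Protocol is misstated or contradicted. As written, Section 10.4.1.2 sets a continuous run of 10 to 12 minutes under a no-blink request with no blink or rest period, and the run feeds a primary endpoint restricted to artefact-free epochs. Some within-session precision is lost at any blink rate above zero.

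The run length follows from the Protocol's own numbers. The size of the loss does not: the 8% to 47% of epochs affected rests on assumed rates of 4 to 15 blinks per minute, a 0.3 s blink and windows of 1.0 to 2.2 s. The consequence for the device comparison and for reliability is smaller than for a single trial average. No minimum epoch count is stated that would be breached.

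**What to change.** First check the EEG Manual. If it already provides blink pauses, say so in Section 10.4.1.2. If not:

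- Split the 300 stimuli into short runs, for example 10 runs of 30. Each lasts about 30 × 2.2 s = 66 s.
- Put a pause of about 10 s between runs in which blinking and resting the eyes are allowed, and restrict the no-blink request to the runs.
- Fix the length of the pauses and make them the same for all four devices and both visits, so that run length does not vary with the device.
- Leave the number of stimuli, their timing and the fixation rule within runs unchanged.

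Cost: 9 pauses × 10 s = 90 s, or 1.5 minutes per device session, which Section 10.4.1 plans at about 2 hours including set-up and clean-up. Over 4 devices × 2 visits = 8 sessions this is 12 minutes per participant, plus a small change to the stimulus script.
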